**2.17 What is the proposed frequency of analyses?**

Analyses will be done after each measurement time and then overall at the end of the data collection –

that is, analyses will be performed post-intervention and after the 9-month follow-up.

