**1.5 How will the results of this trial be used?**

With respect to school practices in multiethnic and disadvantaged neighbourhoods: (1) the program will

help expand and diversify the teaching methods for reducing problem behaviours and improving social adjustment and academic performance of these adolescents; (2) the project will propose group intervention modalities for young people with learning and behavioural problems, organized around three key concepts that underlie the theatre expression workshops: creativity as a means of transforming experience, empowerment through group discussion forums, symbolic and real consolidation of social bonds by building solidarity through shared experiences. These group intervention modalities could complement and, in some cases, replace certain individual treatments that, owing to their potentially stigmatizing nature, are often perceived with distrust, or even avoided, by immigrant families; (3) the project will also confirm the benefits of an integrated approach that involves providing mental health services in partnership with schools when it comes to developing culturally appropriate prevention programs. Transfer of knowledge will rely on dissemination strategies developed by the team to support teachers’ implementation of the creative workshops in regular and welcoming classes (92). School partners and education and health decision makers will be regularly informed through the advisory committee. Preliminary results will be discussed through videoconference at the local, provincial and national levels. A provincial workshop and a national seminar, bringing together representatives of schools and health services will be organised the last year.

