**2.4 What are the proposed methods for protecting against other sources of bias?**

The questionnaires will be filled in by the students themselves in class and by teachers who are not the

homeroom teachers. The teachers who fill in the questionnaires for each student will thus not be present in class with the students for the activity. Even if it cannot be guaranteed that these teachers will be blind to the experimental or control status of the students, given that the students can comment on their activities, they will not be involved in the activities. Lastly, educational achievement is an unbiased source of evaluation, as school marks are given by several different teachers and therefore do not depend solely on the teacher who is in attendance during the activity. At T2, all the teachers involved will be completely blind to the experimental status of the youth. Contamination is another possible bias. The theatre intervention is however quite complex and in our experience has never been implemented spontaneously by teachers who were willing to try it, after discussing with their colleagues. In the case of the tutoring intervention, the added manpower (two resource teachers) is something every teacher in special class would wish to have, but cannot implement independently.

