**2.7 What is the proposed frequency and duration of follow-up?**

Data on the evaluation of the effects of the theatre expression workshops on the students will be

gathered pre- and post-intervention, as well as at follow-up nine months after the end of the intervention. Whenever feasible, the evaluation of the maintenance of the effect of psychosocial interventions for some time (classically 6 months) after termination is a good indicator of their efficacy (34, 36). In the present case, a six month follow up would have resulted in a T2 measure in September, at the beginning of the next school year. This would not have enabled us to assess the medium term effect of the intervention on school performance because the first report card is in November. Furthermore, the teachers’ report Strength and Difficulties Questionnaire (SDQ) is more valid when teachers have been working with the youth for a few months. For these reasons we decided that T2 would be taking place at the beginning of December, 9 months after the end of the intervention. The evaluation questionnaires for each measurement time will be filled in during a 90-minute class period and will be designed so that students with learning difficulties can complete them in approximately 45 minutes. Theoretically all the students taking part will have another school year to finish (high school graduation is at the end of grade 11 in Quebec). However, the youth older than 16 years old who present behavioural and academic difficulties are more at risk to drop out of school than their peers. Nonetheless, in our past studies, the losses attributable to follow-up during a school year have been minimal (< 5%). We therefore do not expect a significant attrition at T2. Special measures will be taken to keep contact with the students who may leave the school at the end of academic school year. Families, who have recently immigrated, are quite mobile. To address potential attrition linked to moving, youth will be asked at T1 if they plan to remain in the same school and/or to move and if so, what is the name of their future school and/or there

new address. Permission to contact them in the future will be requested and contact information for the student will be obtained.

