**2.20 Estimated cost and duration of the trial**

The estimated cost of the proposed randomized trial is 573,819$ spread over 3 years, which is the

planned duration of the study (one year of field work; pre- and post-trial, T0 and T1), another year for

the follow-up (T2) and analyses, and a third year for finalizing the analysis, the transfer of knowledge and dissemination). This estimated cost is detailed in the budget justification.

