
**3.3 Steering Committee of the trial:** This Committee will include 1 school-staff representative of each of the participating schools and 3 representatives of community (organisations and representative from school boards and Quebec department of education in order to discuss any emerging problems.

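### Section 2.4 claims complete blinding of teachers at T2 without a mechanism, and no embargo keeps T1 results from school staff before T2 ratings and marks

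*Protocol*

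**What the plan says.** **Blinding (Protocol 2.4).** Student questionnaires are completed by teachers other than the homeroom teacher, who are not in class during the activity. On whether they know allocation, the section opens with a concession: "Even if it cannot be guaranteed that these teachers will be blind to the experimental or control status of the students". The reason given is that students can talk about what they do. For follow-up the claim becomes absolute: "At T2, all the teachers involved will be completely blind to the experimental status of the youth". No procedure is described.

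**Timing (2.17, 2.7).** "Analyses will be done after each measurement time and then overall at the end of the data collection". Follow-up was set so that "T2 would be taking place at the beginning of December, 9 months after the end of the intervention", which is in the next school year.

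**Information to schools (1.5, 3.3).** "School partners and education and health decision makers will be regularly informed through the advisory committee". Also: "Preliminary results will be discussed through videoconference at the local, provincial and national levels". Neither sentence has a date or a condition. Section 3.3 describes a steering committee: "This Committee will include 1 school-staff representative of each of the participating schools".

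**Schedule (2.20).** Year 1 holds T0 and T1, year 2 holds T2 and analyses, and the plan then gives "a third year for finalizing the analysis, the transfer of knowledge and dissemination".

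**Marks (2.8/2.9, secondary outcome 4).** All teachers are to be unaware that school performance is a study outcome. The T2 mark is the first report card of the following year, issued in November.

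**The concern.** In this open trial, teacher reports and marks are the sources meant to complement the students' own reports. At T2 their value rests on a blinding statement that the plan asserts but does not secure. If a rater knows the student's arm, and perhaps also the T1 result, teacher-rated symptoms (secondary hypothesis 3) and teacher-rated impairment (secondary hypothesis 4) at T2 could reflect expectation as well as behaviour.

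Marks are exposed by a separate route. Telling schools the T1 results on marks would disclose that marks are an outcome, and so end the blind described in section 2.8/2.9 even if no student's arm were revealed.

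**Working it through.** The plan states no figure on this point, so the check sets the sections side by side.

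**1. Does section 2.4 support its T2 claim?** The route to unblinding that it concedes is that students talk. Nothing in the plan closes that route at T2, because the same students are followed. A change of school year may bring new teachers, which is a plausible reason for the claim, but the section does not give it. Section 2.8/2.9 also notes that schools are small settings in which a teacher may know that some classes receive an intervention.

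**2. Who may rate at T2?** Homeroom teachers are excluded, but the year is not specified. The exclusion can be read as covering a student's current homeroom teacher, or also the one from the intervention year. On neither reading does it clearly exclude a teacher who was homeroom teacher of a different trial class that year. In the theatre arm the homeroom teacher helps to run the workshops (2.2.1), so such a person knows at least one class's allocation.

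**3. How common are trial classes in these schools?** Section 2.3 takes six classes from each school (two per arm):

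| School's special classes | In the trial | Share |
|---|---|---|
| 18 | 6 | 6/18 = 33% |
| 16 | 6 | 6/16 = 38% |
| 11 | 6 | 6/11 = 55% |
| 9 | 6 | 6/9 = 67% |
| 9 | 6 | 6/9 = 67% |
| Total 63 | 30 | 30/63 = 48% |

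Overlap between T2 raters and staff of trial classes is therefore plausible. These shares do not measure how many raters would know an arm, and two of the six classes per school are untreated controls.

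**4. Can T1 results exist before T2?** Yes. Early December less nine months puts the end of the intervention in about early March. T1 questionnaires can be analysed from then, about nine months before T2. T1 marks come from the June report card and T2 marks from the November one, a gap of about five months.

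**5. Can those results reach school staff before T2?** Sections 1.5 and 2.17 contain nothing that prevents it. Section 1.5 assigns only the provincial workshop and national seminar to the last year. The regular information and the discussion of preliminary results are undated. Section 2.20 points the other way, with dissemination in year 3. Early release is therefore possible but not planned in terms.

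**6. Which outcomes are exposed?** Teacher-rated SDQ symptoms and impairment at T2, and possibly T2 marks. The primary outcome is youth-reported impairment from T0 to T1, which is complete before any of this can act.

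**The case against.** The strongest reply is that the harmful sequence is an inference. Section 2.17 says when analyses are run, not who sees them, and a T1 analysis is legitimate because the primary endpoint is then complete. Section 1.5 does not say that preliminary results are T1 results by arm. The only dated schedule places dissemination after T2. Access to interim results may also be governed by a statistical analysis plan that is not shown. All of this stands. A reader might infer that T1 results will be given to schools before T2, but the protocol does not say so.

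Other stronger readings also lack support:

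- **That group results unblind raters.** Section 2.4 concerns each student's status, and a group-level result does not reveal it. Such a result matters only to a rater who learns the arm in another way.
- **That the steering committee is a channel for results.** Section 1.5 names an advisory committee. The steering committee in 3.3 is there to discuss emerging problems, and nothing says that either receives comparative data.
- **That bias would favour theatre, or reach the students' T2 self-report.** The first assumes a favourable T1 result. The second assumes that students are told results. Neither is in the text, and in an open trial students know their own arm anyway.
- **That the bias can be sized against d = 0.50.** Section 2.11 sets that value for the SDQ impairment score in the theatre-control comparison, for which the primary outcome is youth-reported. It is not a target for teacher ratings at T2.

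Existing safeguards deserve credit: raters do not attend the activity, T2 falls in a new school year, and marks come from several teachers. They reduce the risk but do not amount to complete blinding, and the concession in 2.4 remains unanswered.

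**Conclusion.** The point holds in a limited form. The T2 blinding statement in 2.4 is an absolute with no mechanism, next to an admission that undercuts it, and its rater exclusion is unclear about the intervention year. The lack of an embargo in 1.5 and 2.17 is a second, weaker gap: it leaves open a release before T2 that the plan neither schedules nor forbids.

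The reach is two teacher-rated secondary outcomes at T2 and possibly T2 marks. The primary analysis is not affected. The documents give no basis for a size or direction of bias, and none is claimed. The conclusion assumes that no other trial document restricts access to T1 results. If one does, the embargo part falls away and the wording in 2.4 still needs correction.

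**What to change.** **Section 2.4.** Replace the claim of complete blinding with a rule that T2 raters were not homeroom teachers of any trial class in the intervention year. Add one item to the teacher form asking whether the rater knows the student's arm, so that awareness can be reported by arm.

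**Sections 1.5 and 2.17.** State that T1 results by arm stay within the analysis team until the last T2 questionnaire and T2 report card are collected. Before then, committees and schools receive process information only. This also protects the blind on marks in section 2.8/2.9.

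**Cost.** Protocol wording and one form item, with no change to design, sample size or planned analyses. School partners wait about nine months longer for T1 results, which fits dissemination in year 3. The choice of T2 raters is slightly restricted, most noticeably in the two schools where six of nine special classes are in the trial.

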**2.18 Sub group analyses**

Analyses to determine the effect of gender and age will be conducted. In the pilot study, however, there

were no differential effects of treatment in the pilot study based on sex (p = .95) or age (p = .96). Thus, although we will control for a potential effect, we do not expect it to be significant. If classes and schools differ significantly on measured socio-demographic variables describing socio-economic and cultural variables we will include them as covariates in the outcome analysis to control for variation between groups/schools.

**2.19 Pilot studies:** The first and larger pilot study was done on regular and welcoming classes. No quantitative data was obtained in the subsequent piloting of the project in special class (90). Other pilot was recently realized (at the request of Québec Ministry of education) in special classes of under- schooled youth (n = 55). In these classes, the majority of youth have suffered high exposure to trauma and separation. This pilot results confirmed that self-report impairment decreased significantly with the intervention and that the intervention appeared to be more beneficial when exposure to premigratory hardship is high (89).

**2.20 Estimated cost and duration of the trial**

The estimated cost of the proposed randomized trial is 573,819$ spread over 3 years, which is the

planned duration of the study (one year of field work; pre- and post-trial, T0 and T1), another year for

the follow-up (T2) and analyses, and a third year for finalizing the analysis, the transfer of knowledge and dissemination). This estimated cost is detailed in the budget justification.

**3. DETAILS OF TRIAL TEAM**

**3.1 Trial management**

The coordination of the trial fieldwork will be done by [name], Post Doctorate Fellow in

transcultural psychiatry with experience in research coordination and quantitative analysis. She will be in charge of the relations with the schools (scheduling of interventions and date collection) in collaboration with [name] (Drama Therapist) and [name] (Psychologist) who will coordinate the drama workshops and an education PhD student who will coordinate the tutorship intervention under the supervision of [name]. [name] will be assisted by 2 Research Assistants ([name] Student and another student to be determined). Data entry will be completed denominalized. Denominalized Questionnaires (T0-T1-T2) will be kept in locked facilities at the CSSS de la Montagne, accessible only to the research team. Report cards, which cannot be denominalized, will be kept in a locked file and destroyed 5 years after the completion of the study.


**3.3 Steering Committee of the trial:** This Committee will include 1 school-staff representative of each of the participating schools and 3 representatives of community (organisations and representative from school boards and Quebec department of education in order to discuss any emerging problems.
